### Diagnostic criteria

#### Traditional Chinese medicine diagnostic criteria for QS&BSS

To avoid the subjectivity associated with expert syndrome differentiation, a traditional diagnostic method, both TCM syndrome differentiation diagnostic criteria for QS&BSS and the TCM syndrome diagnostic scale for QS&BSS will be used in the trial. A diagnosis of QS&BSS should satisfy the following three TCM diagnostic criteria simultaneously:Expert syndrome differentiation: two deputy chief physicians will make an independent diagnosis by syndrome differentiation. If the patient is diagnosed as having QS&BSS by both physicians, he/she could be enrolled. If the diagnosis is different between the two physicians, another deputy chief physician will contribute to the final diagnosis.TCM syndrome differentiation diagnostic criteria for QS&BSS: primary symptoms and signs are (1) distending pain; (2) tingling sensation; (3) pain in a fixed place; (4) pain aggravated by touch; (5) lumps in the body; (6) irritability; and (7) depression.Secondary symptoms and signs are (1) loss of appetite; (2) dim complexion; and (3) blood spots under the skin. Tongue manifestation involves (1) purplish tongue and (2) petechiae on the tongue.Pulse condition involves (1) unsmooth pulse and (2) string-like pulse.A diagnosis of QS&BSS should include more than two primary symptoms and signs; more than one secondary symptom and sign; and one tongue presentation or pulse presentation.TCM syndrome diagnostic scale for QS&BSS: the TCM syndrome diagnostic scale for QS&BSS will be used to assist with the diagnosis. When the total score is greater than or equal to 20, the patient could be diagnosed with QS&BSS (See Additional file 3: Table S1).

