### Intervention

The participants in the test group will take six granules of XFZYC (0.4 g/granule) twice a day for 7 weeks. The participants in the control group will take six granules of an XFZYC-simulated agent (0.4 g/granule) twice a day for 7 weeks. All drugs will be taken orally after meals. The XFZYC and XFZYC-simulated agents will be provided by Tianjin Hongrentang Pharmaceutical Co., Ltd., Tianjin, China. Although the colour and smell of the contents of XFZYC and XFZYC-simulated agents are not identical, the capsule shell makes the drugs seem less different. All the drugs are concealed in the same sealed and opaque packages. The label of the package contains the drug name, the approval number, functions, usage, dosage, storage conditions, expiration date, and the name of the manufacturer. Participants will be informed that they would be randomly assigned to receive either XFZYC or XFZYC-simulated agents. They will be encouraged to contact the investigators if they have any uncomfortable feeling or if they think the drugs are not helpful. Participants in both groups can continue their prior routine treatments, with the exception of Chinese herbal medicine. The details of these routine treatments will be recorded in the case report forms (CRFs). Details of the study procedures are shown in Fig. 1.

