### Data management and statistical analysis

The clinical data management system (http://www.tcmcec.net/) will be used to collect and manage the data. All data from the completed CRFs will be imported into the system twice by two independent data entry clerks to ensure the accuracy. The database will be locked when the principal investigators and statisticians check the data. The original medical records will be archived and saved in the unit responsible for 5 years after the completion of the trial.

All statistical analyses will be performed by an independent statistician blinded to the allocation, using the Statistical Analysis System (SAS, Version 9.2, Institute Inc., Cary, NC, USA) and assuming a two-sided test and a 0.05 level of significance. Based on the strict principle of intention-to-treat (ITT), the outcome measurements will be analysed using a full analysis set (FAS), which means the data of the participants will be analysed according to their original allocation, regardless of the treatment they actually received, withdrawals, losses to follow up, or crossovers. The last-observation-carried-forward (LOCF) method will be used for missing data, and safety outcomes will be analysed using safety sets (SS). Quantitative data will be analysed using the *t* test and analysis of variance (ANOVA). Enumeration data will be analysed using the chi-square test or non-parametric tests. We will use the paired *t* test to analyse significant differences between pre and post treatment. The total dropout rate in each group will be analysed using the chi-square test or Fisher’s exact test. Moreover, the reasons for dropouts will also be descriptively analysed and compared between the two groups. For the safety analysis, the incidence rate of adverse events will be evaluated using the chi-square test and described in a list.

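### The plan adds a paired pre–post significance test that cannot show an XFZYC effect; within-arm change should be descriptive and inference should rest on the between-arm comparison.

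*Protocol article*

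**What the plan says.** Under Data management and statistical analysis, the protocol article sets all analyses at a common standard, "assuming a two-sided test and a 0.05 level of significance". It assigns a t test and ANOVA to quantitative data, and then adds a paired t "test to analyse significant differences between pre and post treatment". That sentence does not name the variables, does not say whether the test is run within each arm or on both arms pooled, and does not mark the result as descriptive.

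Three other parts of the article bear on what a pre–post change would contain:

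- **Entry.** The section on TCM diagnostic criteria makes a diagnostic-scale threshold one of three requirements that must all hold: "A diagnosis of QS&BSS should satisfy the following three TCM diagnostic criteria simultaneously", and "When the total score is greater than or equal to 20, the patient could be diagnosed with QS&BSS". That scale is Table S1 of Additional file 3.
- **Co-treatment.** Under Intervention, "Participants in both groups can continue their prior routine treatments, with the exception of Chinese herbal medicine".
- **Outcomes.** Under Outcome measures, the scales are a patient-reported scale, a single symptom and sign scale and a pain scale (Tables S2 to S4). The main time points are enrolment and week 7.

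The stated primary objective is the feasibility and acceptability of the outcome measures. The only stated threshold for taking an outcome forward is data completeness of at least 80%.

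**The concern.** A paired test asks whether the mean changed between two visits. It does not ask why. Here several causes of change other than XFZYC are plausible and would act in both arms: placebo response on patient-reported and pain scales, routine treatment that carries on, the natural course of symptoms, and possibly regression to the mean after entry on a threshold. Randomisation against placebo is there to cancel these shared causes. The paired test discards that control, and if it is pooled over arms it also mixes drug and placebo.

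The pilot is meant to inform a definitive trial: which scales to use, and data for its sample size. If a significant pre–post change were read as a response to the drug, a scale could look responsive to XFZYC, or an effect could look established, because of change that would also occur on placebo.

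**Working it through.** **No plan figure to reproduce.** The Sample size section gives 60 per group (2 × 60 = 120) and says that no calculation was possible. There is no SD, expected change or pre–post correlation anywhere. Every improvement size below is therefore an assumption, shown as a range.

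**Inputs from the protocol article.** n = 60 per arm; two-sided α = 0.05; paired t test.

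**Rejection probability with no drug effect.** Let both arms improve by the same d, in units of the SD of the change score. The paired t statistic is then non-central t with df = 59 and non-centrality d√60. The critical value is 2.001. Write p for the probability that one arm is significant. The arms are independent, so both are significant with probability p², and XFZYC alone with probability p(1 − p).

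| d (assumed) | d√60 | p, one arm | both, p² | XFZYC only, p(1 − p) |
|---|---|---|---|---|
| 0.1 | 0.77 | 0.119 | 0.014 | 0.105 |
| 0.25 | 1.94 | 0.478 | 0.229 | 0.249 |
| 0.4 | 3.10 | 0.862 | 0.742 | 0.119 |
| 0.5 | 3.87 | 0.968 | 0.937 | 0.031 |

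With no shared change (d = 0), the chance that XFZYC shows a significant improvement and placebo does not is 0.025 × 0.95 ≈ 0.024.

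The last column cannot exceed 0.25, because p(1 − p) peaks at p = 0.5. The value at d = 0.25 sits almost at that ceiling.

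**Fewer participants.** The Quality control section aims to keep dropout within 20%. If only 0.8 × 60 = 48 per arm contributed, p would be 0.40 at d = 0.25 and 0.78 at d = 0.4. The planned last-observation-carried-forward rule would keep n nearer 60.

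**How much could come from the entry threshold?** The threshold is on the diagnostic scale, not on an outcome scale. Let r0 and r7 be the correlations of the diagnostic score with the outcome at enrolment and at week 7, f the share of screened patients above the threshold, and c the threshold in SD units. The expected regression to the mean, in SDs of the outcome score, is (r0 − r7) × φ(c)/f.

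- f = 0.5, r0 = 0.6, r7 = 0.4: 0.2 × 0.399/0.5 = 0.16 SD.
- f = 0.3, r0 = 1, r7 = 0.6 (the extreme considered): 0.4 × 0.348/0.3 = 0.46 SD.
- r0 = r7: 0.

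Over the assumed range it is 0 to 0.46 SD, and it may be small.

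**Simulation check.** This used 8,000 trials per scenario, 60 per arm, pre–post correlation 0.6 and no drug effect. With the 0.16 SD regression alone, the paired test was significant in the XFZYC arm in 29% of trials. Adding 0.2 SD of shared improvement gave 88%, and adding 0.4 SD gave 99.7%. With no shared change it was 5%. Over the same scenarios, the between-arm test of change rejected in 4.6% to 5.5% of trials, close to the nominal 5% whatever the shared improvement.

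**The case against.** The strongest reply is that the paired test is secondary. The same paragraph plans a t test and ANOVA, the trial is placebo-controlled, and participants are analysed as allocated. Efficacy is not the primary objective, and the 80% completeness rule for keeping an outcome does not depend on the paired test. This stands: the fault is a misleading extra test, not a missing comparison.

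Four stronger readings are tempting, and the documents do not support them.

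- **That the test is stated to be within-arm.** The sentence does not say so. A pooled test would meet the same objection, but the one-arm-only figures would not apply to it. Since the variables are not named, the sentence might even refer to the safety tests done before and after treatment.
- **That patients will improve without the drug.** Nothing in the documents shows this. Improvement can be expected from the design features listed, but its size is unknown.
- **That selection on the outcome guarantees regression to the mean.** The threshold of 20 is on the diagnostic scale. It reaches the outcome scales only through their correlation with that scale.
- **That the trial will claim an effect because one arm is significant and the other is not.** No such rule is stated, and neither the choice of scale nor the search for the inflexion point is tied to the paired test. The one-arm-only probabilities show what that reading would cost if someone made it. The 25% figure is a maximum, falling to 12% at 0.4 SD and 3% at 0.5 SD.

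It can also be said that an analysis plan not shown here may hold further detail. That does not remove the point, because the article itself states an inferential test that should be relabelled or withdrawn.

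**Conclusion.** The point holds as a correctable flaw in a supplementary analysis. The paired test is planned as a significance test without a descriptive limit, and its rejection rate depends on any shared non-drug change as well as on XFZYC. With 60 per arm, no drug effect and an assumed shared improvement of 0.1 to 0.5 SD of change, a per-arm test would be significant in about 12% to 97% of trials (48% at 0.25 SD, 86% at 0.4 SD). XFZYC alone would be significant in 3% to 25%, against about 2.4% with no shared change. The logical point, that pre–post significance is not evidence of a drug effect or of responsiveness to the drug, needs none of these assumptions. The percentages rest on all of them and on per-arm testing.

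**What to change.** Replace the sentence on the paired t test with one that reports mean change and its 95% CI for each arm, labelled as descriptive. State that anything said about an effect of XFZYC, or about a scale's responsiveness to it, rests on the between-arm comparison already planned, adjusted for the enrolment value of the same scale (ANCOVA).

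The scales are already completed at enrolment and at week 7, so no new data, visits or participants are needed. The cost is one sentence.

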There are several types of TCM therapies that are used for treating QS&BSS, including Chinese herbal medicine (CHM), acupuncture, moxibustion, cupping, massage and Qigong therapy. Xue-Fu-Zhu-Yu Capsule (XFZYC), one of the Chinese herbal medicine (CHM) drugs, could perform the function of promoting Qi and activating blood to relieve the symptoms of QS&BSS; its use was approved by the China Food and Drug Administration (CFDA) in 2002. The components of the capsule include the following: *Radix Bupleuri* (chaihu), *Angelica Sinensis* (danggui), *Radix Rehmanniae Recens* (shengdihuang), *Radix Paeoniae Rubrathe* (chishao), *Carthamus Tinctorious* (honghua), peach kernel (taoren), *Fructus Aurantii* (zhiqiao), *Radix Liquiritiae* (gancao), *Ligusticum Wallichii* (chuanxiong), *Radix Achyranthis Bidentatae* (niuxi), and *Platycodon grandiflorum* (jiegeng). XFZYC has been used for the treatment of QS&BSS since it was recorded in the book *Correction on Errors in Medical Classics* 200 years ago. In recent years, a number of clinical trials have focused on the effectiveness and safety of XFZYC in patients with QS&BSS subtype diseases, such as coronary heart disease, hyperlipidaemia, ischaemic cerebrovascular disease, gastritis, dysmenorrhoea, and arthritis [5, 7, 8, 12–14], in terms of the outcomes of relevant diseases. However, evidence for the use of XFZYC to address the *Zhengs* in patients with QS&BSS is lacking. To define and optimise an outcome design for a future, adequately powered, definitive trial to evaluate the effectiveness and safety of XFZYC in the treatment of QS&BSS, a multicentre, randomised pilot trial will be undertaken.

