### Randomisation

A total of 120 eligible participants will be allocated to either the XFZYC group or placebo group in a 1:1 ratio using a block randomisation method. The central randomisation system will be used and performed by the Clinical Evaluation Centre of China Academy of Chinese Medical Sciences, which will also maintain the randomisation lists.

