### Sample size

Due to the lack of preliminary studies on the evaluation of the efficacy of XFZYC for QS&BSS using the traditional Chinese medicine patient-reported outcome (PRO) scale, we could not calculate the appropriate sample size. Therefore, we adopted this pilot study with an appropriate sample size of 60 participants per group. The outcomes of this trial will provide data support for the calculation of the appropriate sample size for future clinical trials.

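### The chi-square test named for adverse-event incidence is uninformative at 60 per arm when events are uncommon; report the risk difference with its 95% interval instead (minor)

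*Protocol article*

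**What the plan says.** Under Data management and statistical analysis, the protocol article sets all analyses on one footing, "assuming a two-sided test and a 0.05 level of significance". Safety outcomes are to be analysed in the safety set. For adverse events it then states that "the incidence rate of adverse events will be evaluated using the chi-square test and described in a list". The section mentions no risk difference, confidence interval or upper bound. Fisher's exact test is named there as an alternative for dropout, but not for adverse events. A general rule in the same section reads "Enumeration data will be analysed using the chi-square test or non-parametric tests", and quantitative data go to the t test and ANOVA.

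On size, the Sample size section says "we could not calculate the appropriate sample size" and then "we adopted this pilot study with an appropriate sample size of 60 participants per group". Allocation is "in a 1:1 ratio using a block randomisation method". The Background gives the pilot's purpose as preparing a later, adequately powered "definitive trial to evaluate the effectiveness and safety of XFZYC in the treatment of QS&BSS". The primary objective of the pilot itself is the feasibility and acceptability of the outcome measures. No expected adverse-event rate appears anywhere in the document.

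**The concern.** A significance test answers whether the observed difference is too large to be chance. With 60 per arm and uncommon events, it will usually return a non-significant result even when the true rate on XFZYC is a multiple of the placebo rate. Such a result carries little information about how large an excess remains possible.

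The pilot is meant to prepare a definitive trial of effectiveness and safety in patients who may continue most of their routine treatment. Planning that trial needs the adverse-event rate in each arm and the uncertainty around the difference. A p-value and a listing supply neither directly, although the data needed are already being collected.

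**Working it through.** **Inputs from the protocol article**
- 60 per arm, 1:1 (Sample size; Randomisation).
- Chi-square test, two-sided 0.05 (Data management and statistical analysis).
- Target of keeping dropout within 20% (Quality control). This gives a pessimistic case of 60 × 0.8 = 48 per arm.

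**Assumptions.** The placebo adverse-event rate is not stated, so a range is shown. The excess is taken as a risk ratio of 2 or 3. The plan gives no power figure to reproduce.

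**Power, exact.** With a and b the numbers of participants with an event in the two arms, the uncorrected Pearson statistic is

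X² = 120(a − b)² / [(a + b)(120 − a − b)].

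Power is the sum of Bin(a; 60, p₁) × Bin(b; 60, p₂) over all (a, b) with X² > 3.841.

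**Power, normal approximation, as a check.** Power = Φ{[d − 1.96·√(2p̄(1 − p̄)/60)] / √([p₁(1 − p₁) + p₂(1 − p₂)]/60)}, with d = p₂ − p₁ and p̄ the mean of p₁ and p₂. For 5% v 10%: (0.05 − 1.96 × 0.0481)/0.0479 = −0.92, so power is 0.18. For 10% v 30%: (0.20 − 1.96 × 0.0730)/0.0707 = 0.80, so power is 0.79.

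| Placebo v XFZYC | Ratio | Approx. power | Exact power | Chance of a miss (exact) |
|---|---|---|---|---|
| 2% v 4% | 2 | 9% | 7% | 93% |
| 5% v 10% | 2 | 18% | 17% | 83% |
| 10% v 20% | 2 | 33% | 33% | 67% |
| 15% v 30% | 2 | 50% | 51% | 49% |
| 20% v 40% | 2 | 67% | 68% | 32% |
| 2% v 6% | 3 | 20% | 18% | 82% |
| 5% v 15% | 3 | 45% | 46% | 54% |
| 6% v 18% | 3 | 53% | 54% | 46% |
| 10% v 30% | 3 | 79% | 80% | 20% |
| 15% v 45% | 3 | 96% | 96% | 4% |

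**Where power crosses 50%.** At 60 per arm the placebo rate is about 15% for a doubling (exact 14.6%, approximate 14.9%) and about 5.5% for a tripling (exact 5.5%, approximate 5.7%). Fisher's exact test moves these limits to about 17% and 7%. At 48 per arm they are about 17% and 6% (exact chi-square), or 20% and 8.5% (Fisher).

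**What an interval would show.** Take 9/60 on XFZYC v 3/60 on placebo:
- X² = 120 × 6² / (12 × 108) = 4320/1296 = 3.33, so p = 0.068.
- Wilson limits are 0.081 to 0.261 for 9/60 and 0.017 to 0.137 for 3/60.
- Newcombe lower limit: 0.10 − √[(0.150 − 0.081)² + (0.137 − 0.050)²] = −0.011.
- Newcombe upper limit: 0.10 + √[(0.261 − 0.150)² + (0.050 − 0.017)²] = 0.216.

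The test is non-significant, while the data are compatible with anything from 1 percentage point fewer to 22 points more participants with an event.

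**Zero events.** With 0/60, the one-sided 95% upper bound is 1 − 0.05^(1/60) = 4.9%.

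**Expected precision.** The approximate half-width of the 95% interval when both arms share rate p is 1.96·√(2p(1 − p)/60): 7.8 points at 5%, 10.7 at 10% and 14.3 at 20%.

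**The case against.** The strongest reply is that little is at stake in this document. The trial is an openly uncalculated pilot, its primary objective is the feasibility of outcome measures, and its only stated criterion for carrying an outcome forward is data completeness. Low power for safety is normal at 120 participants. Serious adverse events are to be reported individually to the lead unit and the ethics committee, so they do not rest on the test. Interval formats are commonly left to a full protocol or analysis plan, and neither is shown. All of this stands, and it is why the point is minor. It does not remove the point, because the article states a method for adverse-event incidence and that method is a significance test. Low power is itself the reason to prefer an interval.

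Three stronger readings are tempting and should not be drawn:
- **That the test misses a doubling or tripling whatever the event rate.** It does not. From a placebo rate of about 15% upward a doubling is found at least half the time, and 10% v 30% is found four times in five. Every adverse event is to be recorded, in patients who keep most of their routine treatment, and nothing shown places the overall rate below these limits.
- **That the chi-square test is the only between-arm method for safety.** It is the only one named for adverse-event incidence. The section's general rules can cover the laboratory, ECG and vital-sign data.
- **That a non-significant result would be taken as reassurance.** The protocol contains no safety conclusion or decision rule tied to the test.

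**Conclusion.** The point holds in a limited form and is of minor weight. The only method named for comparing adverse-event incidence is a chi-square test at two-sided 0.05, alongside a listing. At 60 per arm it is more likely than not to miss a doubling when the placebo rate is below about 15%, and a tripling when it is below about 5.5%. These limits rest on assumed placebo rates, on up to 60 participants per arm in the safety set and on the uncorrected chi-square. They rise somewhat with Fisher's exact test or with fewer participants. Within those ranges a non-significant result cannot exclude a material excess. At any event rate, a p-value alone does not give the definitive trial the rates and uncertainty it needs. A reader might go further and infer that the plan misjudges safety or would declare XFZYC safe on p > 0.05; the document says neither.

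**What to change.** Replace the chi-square evaluation of adverse events with wording such as:

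> *Adverse events and serious adverse events will be summarised by arm as the number and percentage of participants affected, with the risk difference and its 95% confidence interval (Newcombe or exact). Where no event occurs in an arm, the upper 95% bound for its rate will be given. All events will be listed. A non-significant test will not be used to conclude that safety is similar.*

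The change is wording only: it needs no new data and can be made before the database is locked. Its cost is presentational. The intervals will be wide, on the scale of 8 to 14 percentage points either side at event rates of 5% to 20%, so the safety statement will read as less reassuring.

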### Quality control

Quality control will be performed as followsRequest for the investigators:

The investigators must possess the qualifications and abilities needed to conduct the trial and will not be continually changed. The principal investigators will ensure the trial is conducted according to the standard operating procedure. A project manager at each site will be responsible for the quality of the research.2.Quality control throughout the entire process of the trial:

Before the trial, investigators will receive pre-trial training on patient screening, data filling, drug use, adverse event (AE) reporting and other matters. During the trial, the investigators will confirm that the participants have received the drugs on time and record the receipt on the medication record form. Those patients who do not take the drugs at the appropriate time will be encouraged to do so, and their reasons will be recorded in detail. Trial supervisors will visit each site regularly to check the case report forms and informed consent to ensure that the trial is strictly following the protocol. The investigators will take measures (to schedule further visits and follow-ups) to keep the incidence rate of dropout within 20%. The number of withdrawals, dropouts, and cases of compliance will be recorded in detail. The trial data will be entered into the database within 2 weeks of being collected. After the trial, all the data will be checked by the quality controller, principal investigator, and statisticians [2].

